### Statistical analyses

Analysis will be on an intention-to-treat basis using the 6-month follow-up as the initial endpoint. Prior to analysis normality and equal variance of the data will be assessed using a Kolmogrov-Smiranov test (with Lillefors' correction) and Leven median test, respectively. Main and interaction effects for all primary and secondary outcome variables will then be determined by either multi-level modelling or a repeated measures ANOVA and simple ANCOVA with the pre-test for each group used to adjust the post-test. Co-variates that may be used are: site, sex, and child and parent program participation rates (to control for the possibility that the combined effect of DM + PASD program is not just due to an increased number of sessions with researchers). A MANOVA design will also be used to analyse the differences between groups for normal outcome variables simultaneously. Data analysis will be undertaken using SPSS (Statistical Package for the Social Sciences) with differences between treatment groups being considered statistically significant at *p *< 0.05. In addition, bivariate correlation and structural equation modelling techniques will be used to describe relationships among the various dependent and independent variables.

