**Methods/Design:**

Each intervention consists of three components: i) 10-weekly face-to-face group sessions; ii) a weekly homework component, completed between each face-to-face session and iii) three telephone calls at monthly intervals following completion of the 10-week program. Details of the programs' methodological aspects of recruitment, randomization and statistical analyses are described here *a priori*.

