##### (i) Parent focused face-to-face group sessions

This consists of ten 2-hour face-to-face weekly sessions. Behavioural change is targeted during the sessions to reduce total energy and fat intakes, increase fruit and vegetable intake and make healthy beverage and snack choices. Practical advice about food shopping and preparation is provided with the sessions including a diadactic component, group work and practical activities.

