##### (ii) Homework

During the 10-weeks parents are encouraged to implement SMART (specific, measurable, achievable, realistic and time-framed) goals into their home environment [14,15]. These goals, although small, result in important practical changes. Facilitators also encourage all group members to share their weekly successes and challenges with other parents in the program thereby facilitating group empowerment and motivation.

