##### (i) Child-focused group sessions

Children attend ten 2-hour face-to-face weekly sessions. Each week children participate in a variety of activities aimed at improving their mastery of 12 fundamental movement skills (run, jump, leap, hop, slide, gallop, strike, roll, kick, throw, catch, bounce). Each session covers three fundamental movement skills, such that over the course of the 10-weeks each skill is re-visited, although the focus is on more complex components of the skill, in subsequent sessions. Skill mastery is aided by adherence to lesson plans for each skill incorporating several learning stages:

a) contextual stage (questions children as to what games, sports and activities require mastery of the specific skill and how the skill is performed proficiently);

b) exploration stage (allows children to explore the different movement patterns related to the skill using movement concepts such as force, speed, levels and relationships);

c) guided discovery stage (isolates specific components of a skill and using a problem solving approach, guides children to discover the correct way to perform the skill); and

d) skill application stage (applies the skills in small drill activities and modified game contexts).

The various activities included in the program have been purposefully selected and adapted to enable children to experience success in their skill practice in a non-threatening and supportive learning environment. Facilitators utilise key pedagogical strategies to ensure students have fun, improve their skill performance and are motivated to practice. The activities conducted in the PASD program have accessed from a variety of resources [18,19] and are also based on the experience of several of the authors and facilitators who have a number of years of primary school teaching experience.

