### Recruitment

Approximately 200 families with overweight or obese children aged between 5–9 years old are being recruited, three cohorts during 2005 and one cohort during 2006 from the Hunter (population approximately 550 000) and Illawarra regions (population approximately 380 000) of New South Wales, Australia. Recruitment for each cohort commences approximately eight weeks prior to each baseline assessment. Numerous recruitment strategies are employed to enhance recruitment success and include: personalised letters sent to school principals and counsellors inviting them to promote the study within their school and in school newsletters; articles and posters placed in general practitioner (GP) surgeries, shopping centres and public libraries, 'GP Newsletters' and other GP communication networks and in pediatric dietetic departments at local hospitals; and delivery of presentations to both school principals and at pediatrician meetings. The university media units at each site distribute media releases resulting in newspaper articles and radio and television interviews and finally paid advertisements are placed in local newspapers. Interested parents are encouraged to contact the study sites directly via the study phone line. Eligibility is determined using a standardised telephone screening script, which addresses specific inclusion/exclusion criteria (Table 1). Eligible families are then sent an information sheet, detailing each intervention, their anticipated benefits, their required commitment level, the researchers involved in conducting the study and a consent form. Once written consent is obtained the participants are randomized (see Randomization section) to one of the three study arms. Participants are notified of their allocated trial group initially by telephone with confirmation by mail. Finally, recruited participants are sent a medical screen, to be completed by their GP and to be returned at the baseline assessment. Only one child from each family is able to be recruited.

**Table 1 T1:** Inclusion and exclusion criteria for recruitment into HIKCUPS.

**Inclusion Criteria**	**Exclusion Criteria**
• Overweight/obese^1^	• Extreme obesity (BMI *Z*-score >4)
• 5.5–9 years of age	• Known syndromal cause of obesity
• Pre-pubertal (no pubic hair)	• Long term steroid use
• Generally healthy	• Medications associated with weight gain
	• Chronic illness
	• Significant dietary restrictions

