### Sample size considerations

Our proposed sample size is based on the assumption that a 50% reduction in weight velocity over a 12-month period would be considered by the investigators as a successful outcome, changes in BMI (primary outcome variable) of 0.26–0.58 SD can be expected among children over a one-year period with the variation dependent upon age, degree of overweight, and height ([name], personal communication). Using the most conservative of these values (0.26 SD), a sample size of 28 participants in each of the interventions, at each site, would detect a difference in mean BMI SD score of 0.26 at baseline using an independent samples *t*-test at *p *< 0.05 with a statistical power of 0.80. Taking into consideration a 20% dropout a total of 216 participants might need to be recruited.

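### Children are treated in shared groups, but the sample size makes no allowance for grouping and the analysis section leaves open a route that ignores it

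*Protocol article*

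**What the plan says.** **Delivery.** The abstract (Methods/Design) gives every intervention a component of "10-weekly face-to-face group sessions". For the dietary program the text is "This consists of ten 2-hour face-to-face weekly sessions", and for the activity program "Children attend ten 2-hour face-to-face weekly sessions". The combined arm runs both at the same time. Parents in the dietary sessions are encouraged to "share their weekly successes and challenges with other parents in the program thereby facilitating group empowerment and motivation".

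**Allocation.** The Recruitment and Randomization sections describe individual allocation, one child per family, stratified by gender and site. Families enter in "three cohorts during 2005 and one cohort during 2006".

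**Sample size.** Sample size considerations gives "a sample size of 28 participants in each of the interventions, at each site", from an independent-samples t-test for a difference of 0.26 in BMI SD score at p < 0.05 and power 0.80. The total is then raised to 216 for 20% dropout. No ICC, group size or design effect appears.

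**Analysis.** Statistical analyses offers a choice: "multi-level modelling or a repeated measures ANOVA and simple ANCOVA with the pre-test for each group used to adjust the post-test". The possible covariates are site, sex and participation rates. A MANOVA across the normally distributed outcomes is also planned. Neither session group nor cohort appears as a term.

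**The concern.** This is an individually randomised trial with group treatment in every arm. Once allocated, families attend ten sessions with the same other families. A cohesive group, a disruptive one, or one that is taught particularly well can move all its members in the same direction. In the dietary sessions, mutual influence is an intended mechanism.

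If outcomes within a group are positively correlated, the variance of an arm mean is larger than the independent-observations formula gives. A repeated measures ANOVA, ANCOVA or MANOVA without a group term then reports standard errors that are too small, and tests of the arm contrasts reject too often. A sample size built on the same independence assumption promises more power than that comparison delivers. At stake is the reliability of the p < 0.05 criterion for every comparison between programs.

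**Working it through.** **1. The plan's own figure.** The protocol gives no SD for the BMI SD score, so 28 cannot be reproduced from stated inputs. Working backwards with a two-sided t-test at 0.05 (sidedness is not stated) and 80% power for a difference of 0.26:
- 28 per arm implies an SD of about 0.34;
- if 56 per arm over both sites is the intended basis, the implied SD is about 0.49.

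For the total, 3 arms × 2 sites × 28 = 168, and 168/0.8 = 210. The stated 216 (36 per arm and site) is within 3% of this. The margin is for dropout only.

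**2. Assumed group structure.** Assume one session group per arm, site and cohort, with each cohort run at both sites: 3 × 2 × 4 = 24 groups. Completers per group: m = 168/24 = 7. The ICC range of 0.01 to 0.10 is also an assumption.

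**3. Formulas.**
- Design effect: DE = 1 + (m − 1) × ICC.
- The naive standard error is too small by a factor √DE.
- True error of a nominal 5% test: 2[1 − Φ(1.96/√DE)].
- Power: noncentral t with noncentrality 0.26/(SD × √(2·DE/n)).

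**4. Results at m = 7.** The two power columns use SD 0.34.

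| ICC | DE | √DE | True error | Power, 28 per arm | Power, 56 per arm |
|---|---|---|---|---|---|
| 0 | 1.00 | 1.00 | 5.0% | 80% | 98% |
| 0.01 | 1.06 | 1.03 | 5.7% | 78% | 97% |
| 0.05 | 1.30 | 1.14 | 8.6% | 69% | 94% |
| 0.10 | 1.60 | 1.26 | 12.1% | 60% | 89% |

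Example for ICC 0.05: DE = 1 + 6 × 0.05 = 1.30; 1.96/√1.30 = 1.72; two-sided tail area 8.6%.

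If 80% was meant for 56 per arm (SD 0.49), the loss is the same as in the 28-per-arm column. Dividing n by DE, instead of inflating the variance, gives 59% rather than 60% in the last row.

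**5. Sensitivity to group size.** With m = 216/24 = 9, ICC 0.05 gives DE = 1 + 8 × 0.05 = 1.40 and a true error of 9.8%. With m = 14 (half as many groups), it gives DE = 1.65 and 12.7%. At m = 14 and ICC 0.10 the pooled 56-per-arm power is about 75%, so the reassuring right-hand column depends on small groups.

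**6. Degrees of freedom.** With 24 groups there are 8 per arm, so a two-arm contrast has about 16 − 2 = 14 degrees of freedom at group level. A correct test therefore loses some power beyond the design effect. On the 56-per-arm, SD 0.49 reading, power is about 72%, 64% and 55% for the three ICCs.

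**The case against.** A reader might infer that the plan is bound to an analysis assuming independence. It is not. Multi-level modelling is the first option named, and it is a standard tool for clustered data. Its levels, random effects and degrees of freedom are details that an article commonly leaves to a statistical analysis plan, so their absence is not held against it. What stands is that the protocol itself accepts the ANOVA/ANCOVA route as an equal alternative and adds a MANOVA, and neither is described with any term for grouping.

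A reader might also infer that the trial is underpowered. The protocol does not support that without a condition. Site is listed as a possible covariate, which suggests a pooled analysis. If 28 per arm was meant to power each site alone, the pooled comparison stays above 80% over the ICC range shown at 7 per group. The protocol does not say which comparison the 0.80 refers to. This limits the power claim only; the understated standard error applies to the pooled test too.

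The size of the effect rests on an ICC and a group structure that are not in the text, and at ICC 0.01 it is small. Shared facilitators within each group are not stated, and mutual motivation is described for the dietary sessions only. Much of the program is worked on by each family: goals, home practice and telephone calls. Teleconferences, content forms and independent review of a third of sessions limit variation in delivery. All this may lower the ICC, but none of it shows that it is zero.

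**Conclusion.** The point holds in a limited form. The sample size makes no allowance for group delivery, and the analysis section leaves open methods that would understate standard errors for any positive within-group ICC. With 24 groups of about 7 completers, the true error of a nominal 5% test would be roughly 6% to 12% for ICCs of 0.01 to 0.10. The loss of power is real for the comparison as sized, but the pooled comparison may keep more than 80%, depending on what 28 per arm was meant to achieve. The direction of the error follows from the design and the methods named. Its size depends on assumed values, so confidence is moderate. The point deserves correction, since a suitable method is already among those the protocol names.

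**What to change.** - Commit to the multi-level option for the arm contrasts, with session group (arm × site × cohort) as a random effect; baseline value, site and sex as fixed effects; and small-sample degrees of freedom.
- Drop the ANOVA/ANCOVA alternative for those contrasts, and do not rest claims about arm differences on the MANOVA.
- Record a session-group identifier for each family. The protocol says that attendance records are kept, but not that they hold one.
- State which comparison the 0.80 power refers to (one site or both pooled) and the SD behind it. Restate that power over an assumed ICC range such as 0.01 to 0.10, with the group size used.

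No extra enrolment is asked for, and treatment and visits do not change. The cost is one more data item, a revised model statement, somewhat wider intervals and possibly a lower stated power.

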### Study interventions

#### 1. The parent-centered Dietary Modification program (DM)

The DM program was designed specifically for parents, as parents of young children play a pivotal role in facilitating changes in a child's food choice, intake and behaviors and are the major role models for healthy lifestyle behaviors [9]. The DM program is based on the Health Belief Model and assumes that parents will make the recommended actions to modify the food behaviors relevant to their family members if they feel that doing so will help to control their child's weight problems and avoid obesity-associated complications [10]. It emphasizes making small changes daily, building on success and developing supporting factors to achieve a sustainable healthy family-eating pattern. Goal setting, problem-solving, role-modeling and positive reinforcement are used to manage changes in food behaviours and strategies incorporated to help parents increase their confidence in making changes related to their goals. The structure and content of the program uses a cognitive behavioral, solution-focused approach from the emerging field of health coaching [11-13].

The DM program has three major components:

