#### 3) The DM/PASD program

The third intervention involves a combination of the DM and PASD programs whereby the children participate in the PASD program at the same time as their parent(s) participate in the DM program.

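### Participation rates, measured after randomisation, are allowed as covariates in the intention-to-treat between-arm models and are not labelled explanatory

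*Protocol article*

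**What the plan says.** All points are from the protocol article.

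- **Analysis principle (Statistical analyses):** "Analysis will be on an intention-to-treat basis using the 6-month follow-up as the initial endpoint".
- **Covariates (same section):** "Co-variates that may be used are: site, sex, and child and parent program participation rates". They are offered for the models that estimate main and interaction effects on all primary and secondary outcomes. Adjustment for the baseline value of the outcome is already planned there.
- **Purpose of the participation covariates (same section):** "to control for the possibility that the combined effect of DM + PASD program is not just due to an increased number of sessions" with researchers.
- **DM arm:** "The DM program was designed specifically for parents", and of its group component, "This consists of ten 2-hour face-to-face weekly sessions". Children have no sessions.
- **PASD arm:** "Children attend ten 2-hour face-to-face weekly sessions", plus one 2-hour refresher. Parents have two 1-hour workshops, at the first and last sessions.
- **Combined arm:** "the children participate in the PASD program at the same time as their parent(s) participate in the DM program".
- **Timing:** families are randomised once consent is given, before baseline assessment (Recruitment). Attendance is recorded during the programs, and a separate analysis relating sessions attended to outcome change is foreseen (Other measures).

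**The concern.** Site and sex are fixed before allocation and are the stratification factors. Participation is different in kind: it follows allocation and is part of what each arm delivers. An arm coefficient from a model that holds participation constant does not estimate the effect of being allocated to that arm, which is what intention-to-treat promises.

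Two errors become possible. If a program works because families attend it, adjustment removes the benefit under test. If motivated families both attend more and do better anyway, adjustment can produce a difference between equally effective programs.

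The covariates also cannot do the job given to them. No family in a single-program arm was offered the combined arm's exposure. Separating extra contact from combined content would therefore rest on extrapolating non-randomised differences in attendance within arms.

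The contrasts at risk are combined versus DM and combined versus PASD. Because use is optional and the model is unlabelled, whichever version is run could be reported as the trial's intention-to-treat result.

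**Working it through.** **1. Sample-size inputs.** Sample size considerations gives 28 per arm per site, so 28 x 2 = 56 per arm and 28 x 6 = 168 in total. With 20% dropout, 168 / 0.8 = 210, against 216 stated (6 / 216 = 2.8% apart); nothing here turns on that gap. No outcome SD is given. Detecting 0.26 with 28 per group, 80% power and two-sided 5% (sidedness assumed) implies SD = 0.26 x sqrt(28/2) / (1.960 + 0.842) = 0.347. The simulation uses 0.35.

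**2. Full attendance, session counts.** Sessions offered, leaving out the refresher:

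| Arm | Child | Parent |
|---|---|---|
| DM | 0 | 10 |
| PASD | 10 | 2 |
| Combined | 10 | 10 |

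With arm indicators, child = 10 - 10 x DM and parent = 10 - 8 x PASD. Both covariates are exact linear functions of arm. A model with an intercept, two arm terms and two counts has five columns but rank 3, so the adjusted contrasts cannot be estimated. Adding the refresher or counting hours changes the constants, not the rank. Within-arm variation in attendance is all that makes the model estimable.

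**3. Incomplete attendance, session counts.** Simulation with 1,000 runs per setting, 56 per arm and least squares of outcome on arm, with and without the two counts. Assumptions not in the documents: attendance of 60-90% for a family of average motivation, logit of attendance rising by 1.0 per SD of motivation, and residual SD 0.35.

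Arm explains 65-92% of the variance in child sessions and 54-87% in parent sessions.

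*Benefit acts through sessions (-0.02 BMI z per session), combined versus DM:*

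| Attendance | Unadjusted (SE) | Adjusted (SE) | SE ratio |
|---|---|---|---|
| 60% | -0.117 (0.067) | 0.003 (0.108) | 1.61 |
| 70% | -0.139 (0.067) | 0.001 (0.124) | 1.85 |
| 80% | -0.155 (0.067) | -0.002 (0.151) | 2.25 |
| 90% | -0.170 (0.067) | 0.007 (0.217) | 3.27 |

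As a check, the unadjusted SE should be about 0.35 x sqrt(2/56) = 0.066. For combined versus PASD, -0.09 to -0.14 also falls to about 0, with SE ratios of 1.4 to 2.6. A weaker link between motivation and attendance leaves less within-arm variation and takes the combined-versus-DM ratio to about 4.3 at 90%.

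*No treatment effect, motivation lowers the outcome by 0.1 per SD, combined versus DM:*

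| Attendance | Unadjusted | Adjusted (SE) |
|---|---|---|
| 70% | 0.004 | 0.164 (0.126) |
| 80% | 0.000 | 0.205 (0.153) |
| 90% | 0.002 | 0.287 (0.221) |

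The sign makes the combined program look worse. The bias is about 1.3 adjusted standard errors (0.164 / 0.126; 0.287 / 0.221). Varying the motivation effect from 0.05 to 0.15 per SD, and the attendance link, gives about 0.06 to 0.48.

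**4. Share of offered sessions attended.** With one share covariate and the same attendance propensity in every arm, the adjusted combined-versus-DM contrast stays within 0.01 of zero when there is no effect. It stays at about -0.15 under the dose effect, as without adjustment. The SE is unchanged at 0.065 to 0.070.

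**The case against.** The wording is permissive, and its parenthesis gives an explanatory purpose. The section opens with intention-to-treat and nowhere makes the participation-adjusted model primary, so it can be read as an intention-to-treat comparison plus an optional explanatory model. This stands as far as it goes: the fault is that the two roles are not separated, not that the protocol commits itself to a wrong primary analysis. A reader might infer such a commitment, but the text does not support it.

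A reader might also infer that participation is fixed almost entirely by arm. That holds for sessions offered, and less so for counts attended when attendance is low. It does not hold for a share of offered sessions, which step 4 shows can be nearly harmless. The protocol does say rates, and Other measures lists participation rates apart from attendance records. Against that, the stated aim of ruling out a result "not just due to an increased number of sessions with researchers" calls for counts. A child's share is undefined in DM, where no child sessions are offered. A share does not measure the number of sessions, and it remains post-randomisation, with bias possible if attendance differs by arm.

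The simulated sizes are fairly challenged. The protocol gives no attendance, dose or motivation figures, and the fall to zero follows from placing the whole effect in sessions.

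Two further inferences go too far. The Study aim compares three strategies without ranking the contrasts, so combined versus single cannot be called the trial's main question. And leaving site and sex as possible covariates is not itself an error, since an analysis plan that is not shown may settle the final set.

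**Conclusion.** The point holds in this form: the protocol allows a post-randomisation covariate in the models that carry its intention-to-treat comparison and does not label that use explanatory.

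If participation enters as session counts, the reading that the stated purpose favours, the adjusted contrast is not the intention-to-treat effect. It can remove a real combined-versus-single difference or create a false one through family motivation. It also inflates the standard error, illustratively about 1.6 to 4 times for combined versus DM at 60-90% attendance. The rank problem at full attendance and the change of estimand follow from the design. The sizes depend on the assumed attendance, outcome SD, dose effect and motivation effect.

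If participation enters as a share, the numerical distortion may be small, but the covariate is still post-randomisation and misses its stated purpose. On either reading, the design cannot separate extra contact from combined content. The harm arises only if the option is used for the main contrasts, which the present wording allows.

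**What to change.** - Remove child and parent participation rates from the covariates of every intention-to-treat between-arm model.
- Keep the baseline-value adjustment already planned, and include the stratification factors, site and sex, in the model.
- Use participation only in the dose analysis foreseen under Other measures, or in a mediation analysis labelled exploratory. Define there whether it is a count or a share, and how DM children are handled.
- State that the combined-arm effect includes its extra contact time and that this design cannot separate the two.

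The cost is a change of wording; no new data are needed. The downside is that the trial gives up a contact-adjusted claim about the combined program, which the design cannot support.

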### Outcome measures

The primary outcome measures for the HIKCUPS trial are Body Mass Index (BMI) *Z*-score and waist circumference. The secondary outcomes include: metabolic profile (blood pressure and fasting levels of total cholesterol, HDL and LDL cholesterol, triglycerides, glucose, insulin and C-reactive protein), dietary intake (mean daily intake or core and non-core foods) and Child Feeding Questionnaire [20], fundamental movement skill proficiency and perceived competence, objectively measured physical activity, time spent in sedentary activities, proficiency in performing an activity of daily living (sit-to-stand transfer), and health-related quality of life. Outcome measures are assessed at baseline and at 6-, 12- and 24-months. The data collection methods for each outcome measure are described below.

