### Randomization

To randomly allocate participants to one of the three intervention groups the bias coin method of allocation, using a computer-based random number-producing algorithm, is used. This method ensures an equal chance of allocation to each group. Stratification by gender and site is done to ensure an equal representation in groups at each site. Only one study member at each site has access to the allocation codes and these are stored on a password-protected computer.

The study has no control group in the conventional sense of 'no treatment', 'waiting list' or 'typical care'. There were two compelling reasons for this: (i) every child who is overweight is deserving of an intervention and is unlikely to remain at a stable level of overweight [28] providing a strong ethical case against a non-intervention control group; and (ii) extensive recent publicity related to childhood obesity has markedly increased awareness and 'no intervention' is likely to be unacceptable to participants potentially resulting in poor retention and follow-up, thus compromising the study integrity. The flow of all participants following recruitment and randomization is summarized in Figure 1.

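### Two primary outcomes are tested at a flat p < 0.05 with no rule for which outcome, visit or contrast carries the primary claim, so 5% does not hold for a claim made if either outcome succeeds

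*Protocol article*

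**What the plan says.** All references are to the protocol article.

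- **Outcome measures.** The sentence beginning "The primary outcome measures for the HIKCUPS trial are Body Mass Index (BMI" goes on to list the Z-score and waist circumference, so there are two primary outcomes. The section adds: "Outcome measures are assessed at baseline and at 6-, 12- and 24-months".
- **Sample size considerations.** This section refers to "changes in BMI (primary outcome variable" and does not mention waist circumference. It reasons from weight velocity over 12 months and uses a two-group t-test at p < 0.05.
- **Recruitment and Randomization.** Children are allocated "to one of the three study arms", and of the allocation method it is said: "This method ensures an equal chance of allocation to each group". There is no conventional control group, and no arm is named as the reference.
- **Statistical analyses.** The analysis is by intention to treat, "using the 6-month follow-up as the initial endpoint". The test structure is given as: "Main and interaction effects for all primary and secondary outcome variables will then be determined by either multi-level modelling", or by repeated measures ANOVA and ANCOVA. A MANOVA is added alongside these, not placed before them as a condition. The criterion is "differences between treatment groups being considered statistically significant at" p < 0.05.

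**The concern.** Two sections disagree on how many primary outcomes there are, and two sections point to different times (12 months for sizing, 6 months for the first analysis). The significance criterion is a single flat threshold. The article does not say whether one or both primary outcomes must succeed, which visit decides, or which of the three possible arm comparisons is the main one.

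The aim is to compare three active programs. A positive primary finding could therefore be reported on BMI Z-score or on waist circumference, for any pair of programs and possibly at any of three visits, each time as significant at 5%. The 5% would describe each test and not the claim that one program is better than another.

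**Working it through.** **The plan's own figure.** The article states no family-wise error rate. Its one related figure is the recruitment target: 28 per arm per site with 20% dropout is 28 / 0.80 = 35, and 35 x 6 cells = 210, close to the stated 216 (36 per cell). This confirms that sizing rests on one BMI comparison between two arms at p < 0.05, with no allowance for a second outcome or further contrasts.

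**Inputs from the article.** Two primary outcomes; three arms with equal allocation, hence three pairwise contrasts; three follow-up visits; p < 0.05 (two-sided assumed).

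**Inputs assumed.** The BMI-waist correlation is not given and is varied over 0.5 to 0.9. The between-visit correlation is not given and is varied over 0.5 to 0.9, taken as equal for every pair of visits.

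**Simple bounds under no difference between arms**
- One overall arm test per outcome, outcomes independent: 1 - 0.95^2 = 9.75%.
- Six independent tests (2 outcomes x 3 contrasts): 1 - 0.95^6 = 26.5%.

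Contrasts that share arms are correlated, and so are the two outcomes, so the actual rates were simulated.

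**Simulation.** 400,000 replicates with three standardized arm means X per outcome and visit, all arms equal.
- Pairwise test: Z = (Xa - Xb) / sqrt(2), rejected if |Z| > 1.96.
- Overall test: Q = sum of (Xa - mean)^2, rejected if Q exceeds the 95% point of chi-square on 2 df (5.99).
- *Ungated*: a claim is made if any pairwise test rejects.
- *Gated*: pairwise tests count only where the overall test for that outcome and visit rejects.

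Reference case, one outcome at one visit: 12.2% ungated, 5.0% gated.

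Two outcomes at 6 months:

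| BMI-waist correlation | Gated | Ungated |
|---|---|---|
| 0.5 | 9.1% | 21.4% |
| 0.7 | 8.4% | 19.7% |
| 0.9 | 7.1% | 16.7% |

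Two outcomes, any of three visits able to carry the claim:

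| BMI-waist correlation | Between-visit correlation | Gated | Ungated |
|---|---|---|---|
| 0.5 | 0.5 | 22.3% | 46.0% |
| 0.5 | 0.7 | 19.6% | 40.9% |
| 0.7 | 0.7 | 18.1% | 37.9% |
| 0.9 | 0.7 | 15.4% | 32.8% |
| 0.9 | 0.9 | 11.7% | 25.9% |

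**Check on a tempting remedy.** Suppose waist circumference is tested at a full 5% once the overall BMI test succeeds. If one arm truly differs on BMI and waist has no effect, the gate is always open. The one remaining null BMI contrast and the overall waist test then each run at 5%. Simulated error over BMI and waist together is 9.3%, 8.8% and 8.0% at correlation 0.5, 0.7 and 0.9. That sequence does not give 5% control across both outcomes.

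**The case against.** The strongest reply is that the article does not describe 18 separate tests. A reader might infer that every pairwise contrast on both outcomes at all three visits is tested at 5%, giving an error of about 33-41% (between-visit correlation 0.7). The text does not support that as a statement of fact. It speaks of main and interaction effects from a model, which are arm-level tests, and it mentions a two-group t-test only for sizing. Under a gated reading the rates are about half as large. One repeated-measures interaction test per outcome gives at most 9.75%. This objection stands against any single headline figure, and the rates above are therefore conditional.

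Second, 6 months is called the initial endpoint, which gives it at least priority in time. If it is the deciding visit, the three-visit figures do not apply to the primary claim. But initial is not primary, and the sizing argument uses 12 months, so the point is not settled.

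Third, a condensed article may leave alpha allocation and testing order to an analysis plan that is not shown. That is fair, and the absence of such detail is not the criticism here. The criticism rests on what the article fixes: two primary outcomes in one section, BMI as the primary variable in another, and a flat p < 0.05. Its abstract also says that the statistical analyses are described there a priori.

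Finally, the MANOVA is a joint test, but the article presents it as an addition and not as a gate, so it protects nothing as written.

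**Conclusion.** The point holds in a limited form. The article contradicts itself on the number of primary outcomes and leaves open which outcome, visit and contrast carry the primary claim, while fixing p < 0.05 for group differences. A claim made when either outcome succeeds has an error rate above 5% on both the gated and the ungated reading. The rate would stay within 5% if both outcomes had to succeed on a single test each, but the article states no such rule.

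The size is about 7-9% (gated) to 17-21% (ungated) if 6 months decides, and about 12-22% to 26-46% if any visit can. These ranges assume no true difference between arms, two-sided tests, BMI-waist correlation 0.5 to 0.9 and between-visit correlation 0.9 to 0.5. The article supplies neither correlation and does not say which testing procedure applies. The defect itself is certain; its exact size is not.

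**What to change.** 1. Reconcile Outcome measures with Sample size considerations by making BMI Z-score the sole primary outcome.
2. Name one primary visit, and reconcile the 12-month basis of the sample size with the 6-month initial endpoint. This is a decision for the investigators and not only a matter of wording.
3. Test the 2-df arm effect on BMI Z-score at that visit at 5%. Only if it is significant, test the three pairwise contrasts at 5% each. With three arms this controls family-wise error for the primary outcome without splitting alpha: if the arms are not all equal, at most one pairwise null can be true.
4. Label waist circumference and the other visits secondary, and claim no family-wise control across BMI and waist.
5. If waist circumference is to stay co-primary, run each outcome's overall test and pairwise contrasts at 2.5%, or use Holm over the six contrasts.

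**Cost.** Either waist circumference loses co-primary status or alpha is split, and an isolated pairwise p < 0.05 without a significant overall test is not claimed. Sample size need not be an obstacle. The article gives no SD, but 28 per group at 80% power for 0.26 implies about 0.341. At 56 per arm (28 x 2 sites), even Bonferroni over six tests would then keep about 91% power for a BMI difference of 0.26. That figure is only as good as the implied SD.
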